## Abstract

**Background:**

Inability to track children’s vaccination history coupled with parents’ lack of awareness of vaccination due dates compounds the problem of low immunization coverage and timeliness in developing countries. Traditional Reminder/Recall (RR) interventions such as paper-based immunization cards or mHealth based platforms do not yield optimal results in resource-constrained settings. There is thus a need for a low-cost intervention that can simultaneously stimulate demand and track immunization history to help reduce drop-outs and improve immunization coverage and timeliness. The objective of this study is to evaluate the impact of low-cost vaccine reminder and tracker bracelets for improving routine childhood immunization coverage and timeliness in Pakistani children under 2 years of age.

**Methods:**

The study is an individually randomized, three-arm parallel Randomized Controlled Trial with two intervention groups and one control group. Infants in the two intervention groups will be given two different types of silicone bracelets at the time of recruitment, while infants in the control group will not receive any intervention. The two types of bracelets consist of symbols and/or numbers to denote the EPI vaccination schedule and each time the child will come for vaccination, the study staff will perforate a hole in the appropriate symbol to denote vaccine administration. Therefore, by looking at the bracelet, caregivers will be able to see how many vaccines have been received. Our primary outcome measure is the increase in coverage and timeliness of Pentavalent-3/PCV-3/Polio-3 and Measles-1 vaccine in the intervention versus control groups. A total of 1446 participants will be recruited from 4 Expanded Program on Immunization (EPI) centers in Landhi Town, Karachi. Each enrolled child will be followed up till the Measles-1 vaccine is administered, or till eleven months have elapsed since enrolment.

**Discussion:**

Participant recruitment commenced on July 19, 2017, and was completed on October 10, 2017. Proposed duration of the study is 18 months and expected end date is December 1, 2018. This study constitutes one of the first attempts to rigorously evaluate an innovative, low-cost vaccine reminder bracelet.

**Trial registration:**

ClinicalTrials.gov NCT03310762. Retrospectively Registered on October 16, 2017.

## Background

Immunization is one of the most cost-effective ways of preventing childhood disability, morbidity and mortality caused by infectious diseases. Despite the substantial advances achieved by governments in establishing and maintaining national immunization systems, immunization coverage is low and delayed, and completion rates are poor in many developing countries. It is estimated that yearly, about 18.7 million infants worldwide are not reached by basic immunization services [1], and over 2 million children die from vaccine-preventable diseases annually [2]. Of the 19.5 million children globally who did not receive 3 doses of DTP vaccine in 2016, around 1.4 million (7%) lived in Pakistan [3] where coverage of Pentavalent 3 remains modest, ranging from below 20 to 80% across regions [4]. While increasing coverage of vaccines remains a priority, timely administration of vaccines remains equally important for success of immunization programs. Increased compliance to vaccine timeliness ensures that children are protected prior to exposure [5] and impacts morbidity through improving population immunity and potential spread of communicable diseases particularly in the form of disease outbreaks [6]. Children who are not vaccinated timely are much less likely to be fully vaccinated at later time due to further delays in subsequent vaccines, a finding corroborated from studies both in developing [5] and developed countries [7].

An increasingly recognized global challenge that leads to stagnating or declining coverage rates and poor timeliness is low uptake and demand for immunization services at the community level. Although the necessity of stimulating caregiver demand for childhood vaccines has been established through extensive research [8–11] developing country governments continue to focus almost exclusively on improving supply. As a result, they often fail to draw on innovative, low-cost public health campaigns to encourage end-users to seek and avail affordable health care. There is a need to develop and leverage demand-side interventions to transform communities from passive to active recipients of immunization services, thus increasing uptake.

This study addresses the gap of low demand for and limited community uptake of immunization services by introducing a simple tool that empowers caregivers by enhancing their awareness of the routine immunization schedule. Although some caregivers may resist immunization, many simply fail to complete a cycle because they are unaware of due dates and required number of vaccination visits, procrastinate, forget [12], or let other priorities get in the way [13]. Investigating effective and innovative ways of improving uptake of routine immunization, this study focuses on one potential channel to stimulate end-user demand: silicone bracelets for children that can serve as effective reminders for parents for timely immunization of their child. These bracelets can potentially save thousands of lives by giving children a chance to complete their immunizations timely. Furthermore, the bracelets can support Pakistan’s vaccine delivery system by encouraging mothers to return on-time for vaccinations without expending resources on campaigns that involve vaccinators combing communities during outreach to remind mothers about due vaccinations.

Currently, immunization cards are used as a systemized way to record and track vaccinations. However, since cardholder prevalence is < 70% in 21 of 33 least developed countries [14] these cards provide an inaccurate coverage estimate and fail to empower mothers who are unable to read and understand the cards. With the recent proliferation of technology and mobile phones, mHealth, particularly digital registries and SMS reminders provide a promising avenue to improve vaccination coverage. However, evidence for such interventions is mixed and limited [15], particularly when taking into account the fact that the majority of unvaccinated children are concentrated in a small number of countries which do not always have the necessary preconditions for mHealth interventions to succeed [16]. Evidence from studies in Pakistan show low response rates to vaccine oriented SMS reminders as well as no impact on self-reported medication adherence for TB. Some of the main barriers limiting the efficacy of mHealth interventions include inability of caregivers to read the messages [17], frequent changing of phone numbers [17, 18] as well as low phone ownership [19] and literacy rates among women who are most often the primary caretakers and responsible for bringing children for immunization. As an alternate to both paper based and technology based reminders, silicone vaccine reminder bracelets are relatively simple and cheap to use without the need for complicated infrastructure and resources. They make use of numbers and symbols to convey the vaccination schedule and immunization status of the child and therefore have the unique benefit of being suitable for illiterate or less educated mothers. Additionally, they can be adapted to most local settings regardless of the spoken language and infrastructure availability; input from vaccinators and mothers can be used to customize the bracelets to meet the needs and preferences of the communities they are introduced in, giving them an advantage over other home-based reminders. Furthermore, these bracelets are simple to use, inexpensive, and baby-safe.

This study aims to rigorously examine the impact of vaccine reminder bracelets on vaccine schedule adherence in a developing country setting, and validate their effectiveness. Two types of bracelets will be evaluated in this study: One developed by Alma Sana Inc., in 2009, and the other a simple silicone bracelet used by Interactive Research and Development (IRD) in a previous project.

### Study objectives

#### Objective 1: Re-design and adapt bracelets

We will conduct a formative study with both mothers and vaccinators through short interviews to inform the redesign of Alma Sana’s bracelet. The Alma Sana bracelet was initially designed for Peru and Ecuador and prior to implementation in Pakistan, the design of the bracelet will have to be adapted to the local context. This will include changes to the color of the bracelet, the symbols used and most importantly, adapting the vaccination schedule on the bracelet to represent the EPI vaccination schedule followed in Pakistan. Questions will therefore focus on preferences for color, size, culturally relevant or meaningful symbols and any other adaptations that would make the bracelet more appealing. Bracelets will then be manufactured accordingly.

#### Objective 2: Evaluate the impact of Alma Sana bracelet in improving immunization coverage and timeliness of Pentavalent-3/PCV-3/Polio-3 and Measles 1 vaccine in intervention versus control arm in Pakistani children under 2 years of age through a randomized control trial

We will conduct an individually randomized, three-arm parallel group design randomized control trial with equal allocation to evaluate the impact of the Alma Sana bracelet. Children in intervention Group A will receive the adapted Alma Sana bracelet, while children in the control group will not receive any bracelets. To evaluate the bracelets’ impact, we will compare our variables of interest (coverage and timeliness rates of (Pentavalent-3/PCV-3/Polio-3 and Measles 1) between Group A and the Control Group.

#### Objective 3: Evaluate the impact of simple silicone bracelet with symbols in improving immunization coverage and timeliness of Pentavalent-3/PCV-3/Polio-3 and Measles 1 vaccine in intervention versus control arm in Pakistani children under 2 years of age through a randomized control trial

We will conduct an individually randomized, three-arm parallel group design randomized control trial with equal allocation to evaluate the impact of the simple silicon bracelet with symbols. Children in intervention Group B will receive the simple silicone bracelet, while children in the control group will not receive any bracelets. To evaluate the bracelets’ impact, we will compare our variables of interest (coverage and timeliness rates of (Pentavalent-3/PCV-3/Polio-3 and Measles 1) between Group B and the Control Group.

### Secondary objective: Compare the immunization coverage and timeliness rates of Pentavalent-3/PCV-3/Polio-3 and Measles 1 vaccine between the Alma Sana and simple silicone bracelets

We will conduct an individually randomized, three-arm parallel group design randomized control trial with equal allocation to compare the immunization coverage and timeliness rates of Pentavalent-3/PCV-3/Polio-3 and Measles-1 between Intervention Group A (given the Alma Sana bracelets) and Intervention Group B (given the simple silicone bracelets). We will compare the efficacy of the two bracelets’ by doing an inter-arm comparison of our variables of interest between Group A and Group B.

## Methods

### Aim

The overall aim of the intervention is improvement in both immunization coverage rates and timeliness among the study participants through introducing simple silicone bracelets as childhood vaccination reminders and trackers.

### Trial design

This will be an individually randomized, three-arm parallel-group trial. The three groups will be equally allocated on a 1:1:1 ratio into two treatment groups and a control group. Children enrolled in the two intervention groups will receive the two different types of bracelets whereas children in the control group will receive no intervention beyond standard care. Figure 1 below shows the study flow.

**Fig. 1 Fig1:**
[figure not shown]
Flow of participants through the study

### Study site and setting

The study will be conducted in 4 Expanded Program on Immunization (EPI) centers located in Landhi Town, Karachi (list of study sites can be obtained from https://clinicaltrials.gov/ct2/show/study/NCT033107620. Centers will be selected based upon the volume of incoming children. Landhi Town is a peri-urban area in the south of Karachi city, in Pakistan’s Sindh province. Karachi is among the 3 districts in Sindh where polio cases have been detected in 2016; within Karachi, Landhi Town is among the highest risk areas for polio prevalence. Landhi Town has an overall estimated population of 872,000 and an annual birth cohort of 30,514 children. The study introduces an intervention designed primarily for illiterate mothers. Landhi Town provides a feasible setting to test the bracelets since the prospective study participants encompass a lower economic stratum, living on $1.25 per day, have low levels of educational attainment, and live in difficult-to-reach areas.

### Participants

Children (male and female) who are 0–3 months old at enrolment, reside in the study catchment area and visit the clinic for BCG or Pentavalent-1/Polio-1/PCV-1 vaccination will be approached for screening to participate in the study.

### Vaccination schedule in Pakistan

The vaccines will be administered as per routine EPI program in Pakistan which include BCG (Bacille Calmette-Guérin) at 0–6 weeks of age, three doses of pentavalent (DPT, HepB, Hib) vaccine, two doses of pneumococcal vaccine (PCV) and three doses of oral polio vaccine at 6, 10 and/or 14 weeks of age, and two doses of measles at 9 and 15 months of age.

### Inclusion and exclusion criteria

Inclusion criteria for the study include children who are (1) presenting to a participating center to receive the BCG or Pentavalent-1/Polio-1/PCV-1 vaccine; (2) accompanied by a primary caregiver; (3) healthy; (4) and (caregivers) have been residing in the study site for more than 6 months. Exclusion criteria include children (1) who are older than 3 months and; (2) whose caregivers plan to go to a different center for the child’s remaining vaccination visits. The study does not involve any vulnerable populations.

### Duration

The study will be conducted over 18 months. Immunization data of all enrolled children will be collected at each vaccination visit following his/her enrolment i.e., when s/he visits for Pentavalent-1 vaccine (if enrolled at BCG) at approximately 6 weeks of age, Pentavalent-2 vaccine at approximately 10 weeks of age, Pentavalent-3 vaccine at approximately 14 weeks of age and Measles 1 vaccine at approximately 9 months old. Participation will continue till the Measles 1 vaccine is administered (recommended age is 9 months), or till eleven months have elapsed since child’s enrolment.

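### Follow-up ends at Measles-1, so third-dose Penta/PCV/Polio coverage, also a primary outcome, is not observed over the same window for every child

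*Protocol article*

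**What the plan says.** The Methods paragraph of the Abstract defines the primary outcome: "Our primary outcome measure is the increase in coverage and timeliness of Pentavalent-3/PCV-3/Polio-3 and Measles-1 vaccine in the intervention versus control groups". The third pentavalent/PCV/polio dose and Measles-1 thus stand side by side as primary.

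The same paragraph fixes the end of follow-up: "Each enrolled child will be followed up till the Measles-1 vaccine is administered, or till eleven months have elapsed since enrolment". Duration repeats the rule: "Participation will continue till the Measles 1 vaccine is administered (recommended age is 9 months"), with the same eleven-month limit as the alternative. The Results section repeats it too. Duration lists the visits in schedule order, with "Pentavalent-3 vaccine at approximately 14 weeks of age and Measles 1 vaccine at approximately 9 months old", and describes no other order.

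The vaccination schedule, given under Vaccination schedule in Pakistan and again at the end of Interventions, sets Measles-1 by age. Neither place makes it conditional on the pentavalent series being complete. On entry age, Participants specifies "Children (male and female) who are 0–3 months old at enrolment".

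Three provisions bear on incomplete data. Under Data collection methods, field workers check past and due vaccines at each visit. After the follow-up phase, phone or in-person interviews collect vaccination data that are missing, and caregivers who did not attend may be contacted. Under Statistical methods, missing data are to be multiply imputed.

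**The concern.** One primary event ends observation of another. The rule is harmless if doses always arrive in schedule order, because the 14-week dose is then settled long before Measles-1. The trial is about children for whom that order may fail. The Background says: "Children who are not vaccinated timely are much less likely to be fully vaccinated at later time due to further delays in subsequent vaccines".

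Consider a child who returns at 9 months with an earlier dose outstanding, is given Measles-1, and receives the third pentavalent/PCV/polio dose at a later visit. The eleven-month window is still open, but participation has ended. A child who never receives Measles-1 is observed for the full eleven months.

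The length of observation for third-dose coverage therefore differs between children according to something that happens after randomisation and that the bracelet is intended to influence. The same applies to full vaccination and drop-out (Table 1) so far as they depend on the third dose. Randomisation does not protect a comparison of arms made over windows of that kind.

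**Working it through.** **1. The plan's own figures.** Inputs from Sample size: two-sided alpha 0.05, power 80%, third-dose coverage 60% vs 70%, Measles-1 coverage 50% vs 60%, drop-out 20%. Using n = (z₀.₉₇₅ + z₀.₈₀)² × [p₁(1−p₁) + p₂(1−p₂)] / (p₂−p₁)², with (1.960 + 0.842)² ≈ 7.849:
- Third dose: 7.849 × (0.24 + 0.21) / 0.01 = 353.2, so 354 per arm.
- Measles-1: 7.849 × (0.25 + 0.24) / 0.01 = 384.6, so 385 per arm.
- Drop-out: 385 / 0.8 = 481.25, so 482 per arm and 1446 in total.

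All three match the article. The point made here does not touch them.

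**2. Time cut off by the rule.** A child enrolled at age e months has a window ending at age e + 11. If Measles-1 is given at age a, the unobserved remainder is e + 11 − a. With a = 9:
- e = 0: 2 months.
- e = 6 weeks (about 1.4 months): about 3.4 months.
- e = 3: 5 months.

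These are the losses when Measles-1 is given at its recommended age. A child who gets it later loses less.

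**3. Whether the sequence can occur.** The first three pentavalent visits are scheduled at 6, 10 and 14 weeks, four weeks apart. If a child's second dose is given at the Measles-1 visit, the same spacing would put the third at a later visit, within the remainder in step 2. If only the third dose is outstanding and it is given at the Measles-1 visit, it is recorded and nothing is lost.

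**4. How often.** The documents give no figure. The expected rates of 60% and 50% are separate marginal rates and say nothing about the order of doses.

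**5. Illustration under assumed losses.** Suppose a share of children have an unobserved third dose and, as a worst case, that dose counts as not received. Observed difference = 10 points + control loss − bracelet loss. Power = Φ{[d − 1.96√(2p̄(1−p̄)/n)] / √([p₁(1−p₁) + p₂(1−p₂)]/n)}, with n = 385 per arm and d the observed difference.

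| Assumed loss, control / bracelet | Observed rates | Difference | Power |
|---|---|---|---|
| none | 60% vs 70% | 10 points | 83.0% |
| 2% / 2% | 58% vs 68% | 10 points | 82.1% |
| 5% / 5% | 55% vs 65% | 10 points | 81.0% |
| 2% / 4% | 58% vs 66% | 8 points | 62.9% |
| 2% / 1% | 58% vs 69% | 11 points | 88.8% |

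First row written out: p̄ = 0.65, (0.100 − 1.96 × 0.03438) / 0.03419 = 0.954, and Φ(0.954) = 0.830.

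Equal loss barely matters. Unequal loss shifts the estimated effect, and the sign depends on which arm loses more.

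**The case against.** The strongest reply has four parts.

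*Scoring.* A reader might infer that an unobserved third dose is scored as not received. No section says so, and the article plans multiple imputation. This stands, and the table above is therefore only a worst-case illustration. Imputation is still not a full answer. It does not replace observing the dose, and it does nothing if the last recorded status is a definite no rather than a blank.

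*Recovery.* The closing interview is not restricted to caregivers who failed to attend, so it may pick up some of these doses. The due-vaccine check would also show, at the Measles-1 visit, that a dose was outstanding. Both points have force. But the interview is for missing vaccination data, and a child who left as planned, correctly recorded as lacking the third dose on that day, need not count as missing. The due-vaccine check looks backward and cannot record a dose given later.

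*Narrow path.* The child must be very late, receive Measles-1, not receive the third dose at that visit, and return again before eleven months. The Background sentence quoted above suggests that late completion is uncommon. This stands, and the number affected may be small.

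*Direction.* A reader might infer that the rule works against the bracelet, because bringing delayed families back for Measles-1 closes their third-dose observation. The documents do not support that as a conclusion. The bracelets are meant to improve attendance at every visit, which could leave fewer bracelet children out of order and push the bias the other way.

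**Conclusion.** The point holds as a weakness in a stated rule. The Abstract, Duration and Results all end follow-up on one component of the primary outcome while another may still be open, and no provision clearly closes the gap. This is not a detail left to a fuller document, because the article itself fixes the rule.

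The size is unknown. The time cut off is 2 to 5 months when Measles-1 is given at 9 months, and less when it is given later. Under the worst-case scoring, equal losses of up to 5% per arm cost about 2 points of power (83.0% to 81.0%). Unequal losses move the observed 10-point difference down or up, for example to 8 or 11 points, but those splits are assumptions and nothing in the documents favours either. The claims that third-dose coverage will be under-counted by a given amount, or that power will fall to about 63%, go beyond the documents.

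Third-dose coverage is affected directly, and full vaccination and drop-out through it. Timeliness is largely untouched, because a 14-week dose given after 9 months is already late. The change is worth making because the window for a primary outcome should not depend on a post-randomisation event, and correcting it is cheap.

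**What to change.** Amend the follow-up rule in the Abstract, Duration and Results so that third-dose status is established for every child over the same fixed window of eleven months from enrolment, whether or not Measles-1 has been given. Specifically:
- Field workers record any later pentavalent, PCV or polio dose given at the centre within that window.
- The closing check of card, register or interview includes every child without a recorded third dose, explicitly including those who already have Measles-1.
- A third dose dated within the window counts as received for coverage, whatever its order relative to Measles-1.

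This changes what is observed, not how any child is vaccinated.

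The cost is a few extra recorded visits and card checks. Field workers are already at the centres throughout follow-up, the study ID is on the child's EPI card, and doses are entered in the card and the register. The timetable allows it: enrolment closed on October 10, 2017, so the last window ends about September 10, 2018, before the expected end date of December 1, 2018.
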